## Abstract

**Background:**

Patients with cervical radiculopathy often have neck- and arm pain, neurological changes, activity limitations and difficulties in returning to work. Most patients are not candidates for surgery but are often treated with different conservative approaches and may be sick-listed for long periods. The purpose of the current study is to compare the effectiveness of neck-specific training versus prescribed physical activity.

**Methods/Design:**

The current protocol is a two armed intervention randomised clinical trial comparing the outcomes of patients receiving neck specific training or prescribed physical activity. A total of 144 patients with cervical radiculopathy will be randomly allocated to either of the two interventions. The interventions will be delivered by experienced physiotherapists and last 14 weeks. The primary outcome variable is neck- and arm pain intensity measured with a Visual Analogue Scale accompanied with secondary outcome measures of impairments and subjective health measurements collected before intervention and at 3, 6, 12 and 24 months after base-line assessment.

**Discussion:**

We anticipate that the results of this study will provide evidence to support recommendations as to the effectiveness of conservative interventions for patients with cervical radiculopathy.

**Trial registration:**

ClinicalTrials.gov identifier: NCT01831271

## Background

Cervical radiculopathy is mainly the result of cervical disc herniation or spondylosis which results in nerve root inflammation, impingement or both. Cervical radiculopathy has an annual incidence rate of 83.2 per 100,000 in the general population [1]. Patients often present with neck pain with radicular distribution in one or both upper extremities often together with paraesthesia, weakness or reflex changes. Certain patients with cervical disc herniation and/or spondylosis may suffer from prolonged functional impairments due to chronic pain, associated activity limitations, long periods of sick leave and difficulties in returning to work [1, 2].

Patients with cervical disc herniation and/or spondylosis suffering from cervical pain and radiculopathy are often treated conservatively [3]. If the symptoms persist and the radiological findings match the clinical symptoms, the patient may be referred for surgery [4]. The scientific evidence for the long term effect of treatment with physiotherapy, drugs or surgery is weak [5–7] and the benefit of surgery compared to conservative treatment is unclear [8]. Consequently, randomised controlled trials using valid and reliable measures to compare surgery with conservative treatment and to evaluate different conservative interventions are needed [9]. Only two prospective randomised controlled trials comparing physiotherapy with surgery have been performed [10, 11]. In the study by Bednarik [11] only patients with a diagnosis of myelopathy were included. Neither of the two studies found a significant difference between treatments at long-term follow-up. Peolsson et al. [12] and Engquist et al. [13] investigated the additional effect of anterior cervical decompression and fusion beyond the effect of a structured physiotherapy program which consisted of neck specific exercises and a behavioural approach in physical function and self-rated outcomes, respectively in patients with radiculopathy due to cervical disc disease. With the exception of less neck pain in the group with surgery plus structured physiotherapy there were no additional benefit at the 2 year follow-up of surgery compared with physiotherapy alone with regard to active range of neck motion, neck muscle endurance, hand related function [12], arm pain, neck specific function rated on Neck Disability Index or general outcome on the Odom scale [13].

The studies evaluating physical treatment for patients with cervical radiculopathy are of various quality [10, 13–22]. The interventions as well as criteria for participation are often poorly described and the number of patients in the trials is small [23]. Additionally, the physical treatment often consists of various interventions and is typically also combined with drugs and other treatments which make it difficult to determine the effects of a single intervention. Four of the studies were prospective randomised controlled trials [10, 17, 19, 21]. In the study by Persson [10] all patients had indications for a surgical intervention and the physiotherapy strategies were pragmatic, involving a number of different treatments. The current conclusion is that randomised controlled trials using valid and reliable outcome measures to compare different conservative interventions is needed [9, 24]. In patients with neck pain of mechanical origin there is evidence that neck specific training may be the single most effective management strategy [25]. In patients with chronic pain, a cognitive approach seems to be effective [26]. However, neither of these approaches has been examined in a patient population with cervical radiculopathy. Patients with cervical radiculopathy often have long-lasting pain before referral to a specialist hence, it is important to test these approaches and to compare them with the general recommendation to stay physically active.

Today, in clinical practice, the waiting times for patients with cervical radiculopathy to be evaluated by a surgeon are long and most of the patients are not surgical candidates. Many patients are therefore sick-listed for long periods of time with various treatment approaches or without any treatment at all. It has been suggested that a structured physiotherapy program should precede surgical intervention [12, 13] but this has not yet been scientifically evaluated.

The purpose of this randomised clinical trial will be to compare the effects of a neck-specific exercise program including a cognitive behavioral approach with prescribed, self-mediated and progressive physical activity approach in patients with cervical radiculopathy. We will include outcome assessment before and after the interventions at 3 and 6 months and 1- and 2 years post base-line.

## Methods

### Design

In a prospective, randomised clinical trial with follow-up at 3 and 6 months, and 1- and 2 years 144 patients with cervical radiculopathy will be included. The study will follow the CONSORT guidelines [27] and has been registered in ClinicalTrials.gov identifier: NCT01831271. The study has been approved of by the Regional Board of Ethics in Stockholm (Dnr 2009/1756-31/4).

### Participant selection

Patients with cervical pain and radiculopathy referred to the Neurosurgery Clinic at the Karolinska University Hospital will be invited to participate. A total of 144 consecutively selected patients will be included. Before inclusion all patients will undergo a standardized physical examination by a physiotherapist which will include a medical history, pain, sensory changes, reflexes, range of motion and muscle strength tests. Inclusion criteria are: 1) Magnetic Resonance Imaging (MRI) verified cervical disc disease showing cervical nerve root compression and 2) neck- and/or arm pain verified with a neck extension test or a neurodynamic provocation test positive Spurling test [28]. Exclusion criteria are: previous fracture or subluxation of the cervical spine, malignity, spinal tumour, spinal infection, previous surgery in the cervical spine, co-morbidity such as disease or symptoms contraindicated to perform the treatment program or the measurements, known drug abuse, lack of familiarity with the Swedish language, diagnosed psychiatric disorder. At the first visit to the physiotherapy department patients who satisfy eligibility criteria will be included if they agree to participate and provide informed consent.

### Sample size

The sample size is based on data from the “Swedish neck study” [12, 13]. A sample size of 56 in each group will have 80% power to detect differences in means of 15 mm assuming that the common standard deviation is 28 mm using two group t-test with a 0.05 two-sided significance level. A drop-out rate of 20% was calculated for.

### Randomisation

After the baseline assessment, each patient will be randomised to one of two interventions: A) active physical rehabilitation with a neck specific exercise program including a cognitive behavioral approach (neck-specific training) or B) prescribed, self-mediated and progressive physical activity (prescribed physical activity). See flow chart (Figure 1). Randomisation will be done in blocks of eight according to a computer generated randomisation list prepared by an independent statistician not involved with subject recruitment. The sequence of allocation to either intervention will be concealed and performed by a person not involved in the testing or treatment of subjects in the project according to the random generated computer list and kept in numbered and sealed envelopes.

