**Flow chart of the randomised clinical trial.**

### Blinding

Group allocation will be concealed until the baseline measurement is completed. The patient will then receive a sealed envelope containing the group allocation. Blinding of the patients, the test leader and the treating physiotherapists participating in the study is not possible. First, because it will be obvious to the patient which the type of intervention they will receive and secondly, because the test leader also serves as contact person for the patients enrolled in the study and the patients could disclose their group assignment. To prevent bias from not blinding the two intervention arms would not be provided by the same physiotherapist or even the same geographical location i.e. prescribed physical activity would be given by physiotherapists other than those giving the intervention neck-specific training. The data transformation from paper questionnaires and physical examination protocols into data files will be handled by an independent person otherwise not involved in the study.

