## Discussion

The importance of the study for patients with cervical radiculopathy as well as society is significant as these individuals often experience severe, neuropathic pain resulting in both great personal and social costs. Many patients are sick-listed for long time periods.

The current study aims to supplement knowledge as to optimal treatment for patients with cervical radiculopathy. Treatment with surgery is also an identified knowledge gap in DUET (Record ID: 381431, published 2010-07-23) however not primarily addressed in the current study but could be effected secondarily as fewer patient might need surgery. The long-term effects of the study could potentially reduce the time of sick leave and improve the rate of patients returning to work and/or former activity by optimising treatments. Furthermore it may decrease the number of patients who will require surgery for their neck problems and thus reduce the mental, physical and societal costs.

The current trial is designed to minimise biases of risk in clinical trials by using randomisation, concealed allocation of patients, specified eligibility criteria and an intention to treat principle in analysis of the data. However, a complete blinding of the patients or the treating physiotherapists is not possible due to the types of intervention where it is obvious which kind of treatment one is receiving. Another potential limitation is that the study does not contain a true control or placebo group. The current patient group have pain and they are referred to the hospital due to their pain and significant findings on MRI. We potentially could have them on a waiting list for 14 weeks but that might result in increasing pain and disability. It would therefore not be ethical to assign some of them to a non-treatment group. Since there is minimal evidence and no consensus of how to best manage patients with cervical radiculopathy there exists considerable variation in what is currently being performed. The treatment differences which will occur in the current study are consistent with those sometimes used in clinical practice.

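### One fixed block size of eight in an open trial leaves up to 20% of allocations deducible before entry, under strong assumptions; varied, undisclosed block sizes remove most of this cheaply

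*Protocol article*

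**What the plan says.** Under Randomisation, the article fixes a single block size: "Randomisation will be done in blocks of eight according to a computer generated randomisation list". An independent statistician outside recruitment prepares the list. A person outside testing and treatment performs the allocation, using numbered, sealed envelopes. Randomisation follows the baseline assessment.

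Under Blinding, it states: "Blinding of the patients, the test leader and the treating physiotherapists participating in the study is not possible". One reason given is that "the test leader also serves as contact person for the patients enrolled in the study", so patients may reveal their group to that person.

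Under Participant selection, patients "referred to the Neurosurgery Clinic at the Karolinska University Hospital will be invited to participate". No other recruiting clinic is named and no stratification is described. It also says: "A total of 144 consecutively selected patients will be included". An unnamed physiotherapist examines each patient before inclusion. One of the exclusions calls for judgement: "co-morbidity such as disease or symptoms contraindicated to perform the treatment program or the measurements".

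The Discussion presents the trial as "designed to minimise biases of risk in clinical trials by using randomisation, concealed allocation of patients", among other protections.

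**The concern.** Sealed envelopes stop anyone from reading the next allocation. They do not stop anyone from working it out. With a constant block size and equal arms, once four patients in a block have gone to one arm, the rest of that block is fixed. In an open trial, earlier allocations can become known to people at the clinic, and the article itself names a route by which this can happen.

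The decision that matters is taken before the envelope is opened. If the person judging eligibility already knows the next arm, that knowledge could colour the judgement-based exclusion, which turns partly on whether the patient can carry out the treatment programme. The two programmes differ a great deal: one is a structured programme three times a week with personal contact, the other is self-mediated activity without scheduled regular contact. Selection of this kind would create baseline differences between the arms. The planned intention-to-treat analysis would not remove them, because it keeps patients in the arm to which they were randomised and does nothing about who was let in.

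**Working it through.** **Inputs**
- Block size 8 (Randomisation).
- Two arms. A 1:1 ratio, hence 4:4 in each block, is an assumption implied by the equal group sizes under Sample size ("A sample size of 56 in each group will have 80% power to detect differences in means of 15 mm").
- 144 patients (Participant selection).
- One running list, assumed because one clinic is named and no stratification is described.

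**The plan's own figure.** A two-sample t-test with difference 15 mm, SD 28 mm, two-sided 0.05 and 80% power needs 55.7, so 56 per group (power 80.2%). Allowing for 20% drop-out, 56 / 0.8 = 70 per arm, or 140 in total. The next multiple of 8 is 144 = 18 × 8, which is 18 complete blocks. The sample size reproduces. The article gives no figure for predictability, so the rest is new calculation.

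**Certain allocations in a 4:4 block.** There are C(8,4) = 70 equally likely orderings. After k allocations one arm is used up in 2 × C(k,4) of them (k = 4 to 7).

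| Allocations made in the block (k) | Orderings with one arm used up | Probability |
|---|---|---|
| 4 | 2 | 2.9% |
| 5 | 10 | 14.3% |
| 6 | 30 | 42.9% |
| 7 | 70 | 100% |

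An observer who knows the block size, the block start and the first k allocations can be certain of every later one in that block once an arm is used up.

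- All earlier allocations known: (2 + 10 + 30 + 70) / 70 = 1.6 per block. 1.6 / 8 = 20.0%; 18 × 1.6 = 28.8 of 144.
- Latest allocation unknown: (2 + 10 + 30) / 70 = 0.6 per block. 0.6 / 8 = 7.5%; 18 × 0.6 = 10.8 of 144.
- Latest two unknown: (2 + 10) / 70 = 0.17 per block. 0.17 / 8 = 2.1%; 18 × 0.17 = about 3 of 144.

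**Best guess.** Always naming the arm with fewer patients so far in the block, with a coin toss at ties, is right for 66.6% of allocations over the 70 orderings (5.33 of 8), against 50% by chance.

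**Varying block sizes.** This was simulated over 144 patients, with each block size drawn with equal probability and an observer who knows the set of possible sizes and all past allocations. The sizes are illustrative assumptions.

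| Scheme | Certain calls | Best-guess rate |
|---|---|---|
| Fixed 8 | 20.0% | 66.6% |
| 4, 6 or 8 | 2.2% | 68.0% |
| 6, 8 or 10 | 1.7% | 66.4% |

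Varying the size removes most of the certainty but hardly changes the best-guess rate. Including blocks of 4 makes guessing slightly easier, so the larger mix is the better choice.

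**The case against.** The strongest reply is that the arithmetic is only an upper bound and the chain leading to harm is not in the document.

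- The 20% needs full and prompt knowledge of earlier allocations. The article says only that patients may reveal their group. Missing one or two recent allocations removes most of the certainty. This stands, and the figure must be given as a ceiling.
- A reader might infer that the test leader screens patients and so can foresee one allocation in five. The article does not say so. The examining physiotherapist is not identified; elsewhere the test leader is described only as a specialised physiotherapist at the specialist clinic. The link is possible but not stated. This stands.
- A reader might also infer that concealment at entry is not secured. That goes too far. An independent list, third-party allocation, numbered sealed envelopes and release only after baseline are all described. Consecutive selection works against delaying a patient's entry, and most of the exclusions are factual. This stands, with one limit: none of these steps prevents deduction from past assignments, and consecutive selection does not prevent an exclusion.
- An article may leave the withholding of the block size from staff to the full protocol. This stands too, so the point does not rest on that silence. It rests on the rule that the article does state, a single constant block size, and on the openness that it acknowledges.
- Varying the block sizes does not lower the best-guess rate materially. This is true, and the fix should not be presented as if it did.

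**Conclusion.** The point holds as a conditional weakness. A single fixed block size of eight in an open and apparently single-clinic trial leaves up to 20% of allocations (about 29 of 144) deducible with certainty before entry. This assumes 1:1 blocks on one running list, and a person judging eligibility who knows the block size, the block starts and every earlier allocation. The share is 7.5% if the latest allocation is unknown and about 2% if the latest two are.

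The documents do not support the stronger conclusion that the test leader controls entry or that concealment has failed. Nor do they allow an estimate of any resulting bias on the pain scale. The change is worth making because it costs little and because the article relies on concealed allocation as a main protection in a trial that is otherwise open. It is a cheap improvement, not a fault that undermines the trial.

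**What to change.** Under Randomisation, replace the fixed blocks of eight with block sizes that vary at random, for example 6, 8 and 10. The independent statistician generates them and withholds them from everyone who screens, tests or treats. If recruitment has begun, apply this to the part of the list not yet used.

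Add that eligibility is decided without reference to earlier allocations and is recorded as final before the next numbered envelope is assigned. The record alone does not stop someone from predicting before inclusion. Keeping knowledge of past allocations out of the eligibility decision is what addresses the best-guess rate, which varied block sizes leave near 66%.

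The cost is a regenerated list and a dated eligibility record, with no added visits or staff. The arms may end slightly unequal if the last block is incomplete: with a largest block of 10, the difference cannot exceed 10 / 2 = 5 patients. In return, certain calls fall from 20% to about 2%.

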**Figure 1 Fig1:**
[figure not shown]
**Flow chart of the randomised clinical trial.**

### Blinding

Group allocation will be concealed until the baseline measurement is completed. The patient will then receive a sealed envelope containing the group allocation. Blinding of the patients, the test leader and the treating physiotherapists participating in the study is not possible. First, because it will be obvious to the patient which the type of intervention they will receive and secondly, because the test leader also serves as contact person for the patients enrolled in the study and the patients could disclose their group assignment. To prevent bias from not blinding the two intervention arms would not be provided by the same physiotherapist or even the same geographical location i.e. prescribed physical activity would be given by physiotherapists other than those giving the intervention neck-specific training. The data transformation from paper questionnaires and physical examination protocols into data files will be handled by an independent person otherwise not involved in the study.

### Evaluation and test procedure

*Background data* that will be collected at the first visit of the study will include: gender, age, social situation, smoking habits, back pain, pain medication, pain history related to the neck problems, previous medical problems (differential-diagnosis to cervical disc disease), earlier treatments for the neck problems and its effects, work situation (such as type of work, workload due to the neck, work satisfaction and sick-leave), and physical activity/ exercise habits.

*Clinical measurements* that will be performed by an independent, blinded examiner before intervention, and at 3, 6, 12 and 24 months follow-up periods: Neurological examination, cervical range of motion [29], neck muscle endurance [30], hand strength [31] and balance [32, 33]. These measurements have good reliability and known reference data.

*Questionnaires* used have good reliability and validity (listed under secondary outcome measures). The questionnaires will be administered before intervention, 3, 6, 12 and 24 months after the start of the intervention.

### Primary outcome measure

The primary outcome measure is pain intensity. Intensity of neck pain and arm pain is measured on a Visual Analogue Scale (VAS) (0–100 mm) [34, 35]. Pain will be measured before intervention, 3, 6, 12 and 24 months after the start of the intervention.

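### The primary outcome names no primary pain score, visit or success rule, so the single powered test is undefined and the 5% error rate is not guaranteed

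*Protocol article*

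**What the plan says.** The Primary outcome measure section states: "The primary outcome measure is pain intensity. Intensity of neck pain and arm pain is measured on a Visual Analogue Scale". It continues: "Pain will be measured before intervention, 3, 6, 12 and 24 months after the start of the intervention". The abstract (Methods/Design) agrees: "The primary outcome variable is neck- and arm pain intensity measured with a Visual Analogue Scale". Neither place names a leading score, a composite of the two, or a leading follow-up.

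The Sample size section describes one test. On group size it says: "A sample size of 56 in each group will have 80% power". The target is a 15 mm gap between the group means, with an SD of 28 mm in both groups. The level of the test is given by the words "using two group t-test with a 0.05 two-sided significance level". The section does not say whether the 15 mm is neck or arm pain, or at which month.

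The Data analysis section describes between-group comparison by intention to treat, with parametric or non-parametric methods chosen by skewness. It gives no primary contrast and no order among the pain scores or visits. The purpose statement at the end of the Background lists all four follow-ups without ranking them.

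**The concern.** Two scores at four follow-ups allow up to 2 × 4 = 8 primary between-group comparisons, while the sample size covers one. A reader of the results could not tell which comparison the 80% power belonged to, or which result decides the trial.

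The choice matters for two reasons.

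- **The visits ask different questions.** The intervention lasts 14 weeks, with therapist contact available to week 20 in both arms. The 3-month visit (about 13 weeks) falls before the intervention ends. Six months is the first visit after support stops. Twenty-four months is about durability.
- **The scores can diverge.** The Background reports that in the earlier surgery-versus-physiotherapy trial the groups differed on neck pain but not on arm pain. The Sample size section takes its data from that same study. A split result is therefore realistic, and this protocol does not say how to read one.

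**Working it through.** **Inputs from the protocol article.** Difference 15 mm, SD 28 mm, two-sided alpha 0.05, 80% power, 56 per group (Sample size); two scores and four follow-ups (Primary outcome measure); 20% drop-out (Sample size); 144 in total (abstract); blocks of eight (Randomisation). The correlations between scores, between visits and with baseline are not given. Those used below are assumptions, shown as ranges.

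**1. The plan's own figure.** Standard error = 28 × √(2/56) = 5.29 mm, so the noncentrality is 15/5.29 = 2.835. The noncentral t gives power 80.2% at 56 per group; the exact requirement is 55.67, rounded up to 56. For drop-out, 112/(1 − 0.20) = 140, and the next multiple of eight is 144. The stated figures reproduce, for one comparison.

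**2. Error rate if any significant test counts as success, each at 0.05.** With independent tests the rate is 1 − 0.95^k:

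- k = 2: 1 − 0.95² = 9.75%
- k = 8: 1 − 0.95⁸ = 33.7%

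With correlated test statistics (multivariate-normal simulation, |z| > 1.96), two scores at one visit give 9.5%, 9.1%, 8.3% and 7.0% at between-score correlations of 0.3, 0.5, 0.7 and 0.9. All eight comparisons give:

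| Between scores | Visits 0.4 | Visits 0.7 | Visits 0.9 |
|---|---|---|---|
| 0.3 | 30% | 24% | 17% |
| 0.5 | 28% | 23% | 17% |
| 0.7 | 26% | 21% | 15% |
| 0.9 | 23% | 18% | 13% |

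**3. If both scores must be significant at one visit.** Alpha stays at or below 5%. The power for one score by the normal approximation is Φ(2.835 − 1.960) = 80.9%. Joint power, if both scores truly differ by 15 mm, is 0.809² = 65% at correlation 0 and 76% at correlation 0.9 (bivariate normal).

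**4. Power of workable rules at one visit, 56 per group.**

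- *One named score, or the first score in a fixed order, at 0.05:* 80.2%. In a fixed order, the second score can be claimed only if the first also succeeds, so its power is the joint figure in step 3.
- *Holm, only one score differs:* that score in practice needs 0.05/2 = 0.025, with power 71.3%.
- *Holm, both differ by 15 mm:* about 76%–77% per score at between-score correlations of 0.3–0.7 (simulation).
- *Baseline adjustment at 0.025:* the SD becomes 28 × √(1 − ρ²). With ρ = 0.3, 0.4 and 0.5 this is 26.7, 25.7 and 24.2 mm, and power is 75.7%, 79.3% and 84.0%.
- *A strict 80% per score at 0.025 without adjustment:* 68 evaluable per group, 68/0.80 = 85 with drop-out, 170 in total.

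**The case against.** A reader might infer that the protocol plans eight primary tests and that its 5% error rate is therefore broken. The documents do not support that. The 0.05 is the level of one planning t-test, and nothing in the article claims a trial-wide 5%. Pain is said to be measured at four follow-ups; separate primary tests at each are not specified. No rule says that any one significant result makes the trial positive. Eight is an upper bound, and the inflated rates in step 2 apply only under an any-success reading that the protocol neither states nor excludes. Under a both-scores rule, or a single repeated-measures contrast, alpha could hold. The size of any inflation also depends on correlations that the article does not give.

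It is also fair to say that a multiplicity procedure and a repeated-measures model commonly sit in an analysis plan, which is not shown. Their absence from the Data analysis section is not the point here.

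What remains is narrower. The article has its own primary-outcome and sample-size sections, and the two do not match: the outcome is several quantities and the powered hypothesis is one unidentified quantity. That is core protocol content. An analysis plan should elaborate the primary hypothesis, not select it.

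**Conclusion.** The point holds in this form: the powered hypothesis is undefined, and the plan as written does not guarantee a 5% error rate. It has not been shown that the rate is exceeded.

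The size depends on the rule that is eventually applied. Under any-success, the range is about 7%–10% for two scores at one visit and about 13%–30% for all eight comparisons (assumed correlations 0.3–0.9 between scores and 0.4–0.9 between visits; independence gives slightly more). Under both-must-succeed at one visit, the error rate holds but power falls to about 65%–76%, short of the stated 80%. The figure of 56 per group is correct for a single named score at a single named visit. Because the gap bears on the primary conclusion, it should be closed before results are seen.

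**What to change.** 1. Name one primary visit and make the other three secondary. Six months is one candidate, as the first visit after therapist support ends at week 20. No passage gives it priority, so the investigators should confirm the choice.
2. At that visit, do one of the following: name one score as primary; test neck pain and then arm pain in fixed order; or test both with Holm at overall two-sided 0.05.
3. In the Sample size section, say which score and visit the 15 mm and SD of 28 mm refer to, and give the power that matches the rule at 56 per group. That is 80% for a single or first-ordered score. Under Holm it is 71% for a score if only that one differs, and about 77% per score if both differ by 15 mm.
4. Consider adjusting for the baseline pain score, which is already collected. It would raise the 71% to about 76%–84% at assumed baseline correlations of 0.3–0.5.

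The cost is wording in the protocol, the analysis plan and the registry entry, with no more patients. The downside is a slightly lower stated power per score if two scores share alpha. Only a demand for 80% per score at 0.025 without baseline adjustment would take the total from 144 to 170.
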